## Abstract

**Introduction:** Patients with Parkinson's disease (PD) often exhibit difficulties with dexterity during the performance of activities of daily living (ADL) due to dysfunctional supplementary motor area (SMA). The aim of this clinical trial protocol work is to describe how the effectiveness of a combined repetitive transcranial magnetic stimulation (rTMS) over SMA and video-game-based skill training (VBT) in PD will be evaluated. The short and long-term benefits are assessed.

**Methods and analysis:** A single-blind (patients) stratified (based on Hoehn & Yahr) parallel randomized sham-controlled rTMS-VBT study with a baseline and two follow-up measurements (3 and 12 weeks) is being conducted. These measurements include the dexterity questionnaire 24 (DextQ-24) as a primary outcome, and nine hole peg test and coin rotation task as main secondary dexterity outcomes. Further secondary outcomes will be the subscale II of the movement disorders society unified PD rating scale (MDS-UPDRS) to assess improvements on overall ADL and the Parkinson's Disease Questionnaire-39 to assess quality of life. Thirty-six outpatients (from one neurorehabilitation center) with PD (diagnosis based on brain bank criteria) will be recruited who report difficulties with dexterity in performing ADL. All PD patients will receive a 45-min VBT three times a week for 3 weeks. The PD patients randomized in the experimental group will receive VBT preceded by real rTMS, being intermittent theta burst (iTBS) stimulation sessions. The PD patients randomized to the control group receive a VBT with sham rTMS.

**Discussion:** The study will provide evidence to determine whether a combined iTBS and VBT skill intervention is more effective than a VBT intervention alone to improve dexterity in PD.

**Ethics and dissemination:** The study was approved by the Ethics Committee for Northwest and Central Switzerland (EKNZ), Switzerland 2019–00433. The study will be conducted in accordance with the Helsinki Declaration and the Guidelines of Good Clinical Practice. Informed consent will be signed prior to subject enrolment. Dissemination will include submission to international peer-reviewed professional journals and presentation at international congresses.

The study protocol has been registered in the clinicaltrials.gov registry with the identification code: NCT04699149.

## Introduction

Patients with Parkinson's disease (PD) often face dexterity-related difficulties, both in performing basic (grooming, buttoning a shirt) and instrumental activities of daily living (ADL), such as cooking a meal, organizing pills in pill holders, and writing (1–4). These difficulties may be present even in early stages of the disease. They further increase the burden of disease and reduce quality of life (QoL) (2). Dopaminergic therapy only slightly improves impaired dexterity (5). Therefore, complementary treatments are needed to reduce its impact on ADL. Previous studies have shown short-term effects (immediately after training) of a particular hand training, either supervised (6) or unsupervised (7). However, no sustainable long-term effects were shown so far. A reason may be that important aspects for an optimized motor learning (8) were not sufficiently targeted, such as the variability of the load, the feedback of the performance over a longer period of time or the level of difficulty.

Video-game-based training (VBT) has been rapidly developing in PD neurorehabilitation (9). VBT is attractive and challenging, and therefore potentially suitable to motivate PD patients over time (10). Other benefits of VBT include the ability to adjust the difficulty of the exercise and to provide online visual and/or verbal feedback during the training. In terms of dexterity, several studies have now shown that VBT was feasible and improved dexterity in PD patients in the short term (immediately after the intervention) (11–14). However, long-term effects of VBT have not yet been assessed.

To further improve training effects in PD, a combination of behavioral interventions with neuromodulation techniques such as non-invasive repetitive transcranial magnetic stimulation (rTMS) has been proposed (15–18). The rationale behind a combined rTMS and behavioral training is that by applying rTMS before training, the brain may reach an optimal state of learning thereby facilitating subsequent training effects (19). The principle of activity dependent neuroplasticity (20) also suggests that combinations of behavioral training with rTMS might have promise in facilitating long term effects (21). We use herein an intermittent theta-burst protocol (iTBS), a type of rTMS, which is expected to produce behavioral effects not only outlasting the single administration (short term), but also retained after multiple applications (long term) (22–24). iTBS has been shown to be facilitatory in nature by increasing cortical excitability (25–27). When applied over primary motor cortex iTBS may enhance either sensorimotor integration (28) or mood (29) in PD patients. Similarly, if supplementary motor area (SMA) was the target region, beneficial effects on overall motor symptoms were shown by using rTMS (24, 30). The SMA also plays a key role in the generation of self-initiated, multisegmental, complex, voluntary finger movements (31, 32). In PD however, SMA activity can be reduced due to decreased positive efferent feedback arising from the basal ganglia–thalamocortical motor loop (33). Consequently, PD patients may show altered activation patterns in the SMA and less cortico–cortical excitability. Indeed, it was shown that a diminished resting state perfusion in the left SMA in PD explained poor dexterous performance, which was measured by a coin rotation (CR) task (34). These findings further attributed to the role of the SMA controlling for fine finger movements. Interestingly, one previous pilot rTMS study in PD already demonstrated a short-term improvement on handwriting, which requires good dexterous function, when patients received one session of facilitatory rTMS over the left SMA (35).

The aim of the present clinical trial protocol paper is to describe how the effectiveness of a combined iTBS-VBT skill 3-week intervention in PD will be evaluated. The short and long-term benefits of this training program will be evaluated. We predict that the use of iTBS before VBT can further strengthen the training effects and possibly also achieve sustainable long-term effects. Therefore, we expect significantly improved dexterity in both the short and long-term, which leads to improved ADL and QoL in patients with PD.

## Methods and Analysis

### Trial Design

A single-blind (patients) parallel RCT with a stratified random intervention distribution is carried out. The random sequence generation using a computer software program is stratified, according to the Hoehn & Yahr (H&Y) scale, Level 1 = H&Y I to Level 4 = H&Y 4, (36) at T0. After stratification, a simple randomization (1–1) occurs within each stratum level (Level 1 to 4). Randomization and treatment allocation is concealed within SecuTrial, which is a GCP-compliant electronic data base system (https://www.secutrial.com/en/), managed externally by the Clinical Trial Unit (CTU) Schweizer Paraplegiker Zentrum (SPZ) Nottwil. After the baseline assessment (hereinafter referred to as T0), all PD patients receive 45-min manual dexterity intervention three times a week for a period of 3 weeks. The PD patients randomized in the experimental group will receive VBT each time, preceded by true iTBS stimulation. The PD patients randomized to the control group receive a VBT with a preceding sham TMS each time (see Figure 1). Patients will be blinded to the rTMS protocol (sham vs. real). This means that patients will not be informed throughout the whole trial whether they received real or sham rTMS stimulation. Follow-up measurements (T1 and T2) are carried out after a period of 3 weeks and 3 months. All data is collected within SecuTrial. The study will be performed according to the CONSORT (Consolidated Standards of Reporting Trials) statement, http://www.consort-statement.org/.

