### Sample Size Calculation

The significance level alpha is defined as 0.05 (two-tailed) for detecting a mean difference between groups on the primary outcome being the Dexterity Questionnaire 24 (DextQ-24) (4) in favor of the real iTBS-VBT dexterity group. Based on previously observed data one may assume a within-group standard deviation of up to 10 points. The study is designed to detect a mean difference of 10 or more points, which exceeds the MDC95 of 8 points found in our validation study (4). A total sample size of 30 evaluable subjects, 15 per group, is required to detect a mean difference of an at least 1.1-fold within-group standard deviation with a target power of at least 80%. Considering a maximal drop-out rate of 15%, we aim to recruit 36 patients in total.

In any case, patients who do not complete the training sessions and/or even decide to drop out of the study for whatever reason will be encouraged to continue to participate in the scheduled assessments for at least T1 (and/or a time point prior to the individual end of the study) and ideally to provide a postbaseline assessment for at least the primary endpoint.

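### Simple randomization within each Hoehn & Yahr level gives the same allocation as no stratification, so as written it secures neither H&Y balance nor near-equal arms

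*Protocol article*

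**What the plan says.** The Abstract calls the trial a "stratified (based on Hoehn & Yahr) parallel randomized sham-controlled rTMS-VBT study". The Trial Design section says that the random sequence "is stratified, according to the Hoehn & Yahr (H&Y) scale, Level 1 = H&Y I to Level 4 = H&Y 4", and then gives the method inside each level: "After stratification, a simple randomization (1–1) occurs within each stratum level (Level 1 to 4"). No block, permuted list or minimization is mentioned; the 1-1 is an allocation ratio, not a restriction. Allocation is concealed in SecuTrial, which an external clinical trial unit manages.

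Under Sample Size Calculation, the plan states: "A total sample size of 30 evaluable subjects, 15 per group, is required". The effect size behind that number is 1.1 SD, at two-sided alpha 0.05 and at least 80% power. Recruitment is set at 36 to allow for 15% drop-out.

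Under Statistical Analysis, the primary ANCOVA contains treatment and baseline DextQ-24. Adjustment for H&Y appears only as a further supportive analysis that may be performed.

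**The concern.** Stratification balances a factor only if allocation is restricted inside each stratum. With an independent draw for every patient, it does not matter whether the draws are filed under four headings or one. The article therefore claims a design property that its stated method does not deliver.

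H&Y stage is the only factor chosen for balancing, and eligibility spans stages I to IV with just 36 patients. If allocation does not balance it and the primary model does not adjust for it, a chance imbalance in disease stage could leave the result of a small trial open to challenge. Allocations already made cannot be rebalanced afterwards. Arm sizes are also left to chance in a trial planned on 15 versus 15.

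**Working it through.** **Inputs.** From Trial Design: four strata, simple 1:1 allocation. From Sample Size Calculation: 36 recruited, 30 evaluable, 1.1 SD, two-sided alpha 0.05, 15% drop-out. From the Discussion: drop-out not expected above 10%. The article gives no H&Y stage counts, so three splits of 36 over stages I/II/III/IV are assumed: 4/16/12/4, 9/9/9/9 and 2/20/12/2.

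**1. The plan's own figure.** Two-sample t test, noncentrality δ = d/√(1/n₁ + 1/n₂), 28 degrees of freedom, critical value 2.048. For d = 1.1 and 15:15, δ = 1.1/√(2/15) = 3.01 and power is 82.8%; 15 is the smallest number per arm that reaches 80%. Drop-out: 30/(1 − 0.15) = 35.3, rounded up to 36. The stated sample size reproduces.

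**2. Equivalence.** Let stratum k hold n_k patients. Simple randomization puts Binomial(n_k, ½) of them in the experimental arm, independently across strata. Unstratified simple randomization gives exactly the same counts for each stage. In both cases the arm total is Binomial(36, ½) and the SD of the arm-size difference is √36 = 6. Simulation with the 4/16/12/4 split (100,000 runs) agrees within simulation error:

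| Event | Simple within strata | No strata |
|---|---|---|
| Some stage differs by 4 or more patients | 74.5% | 74.3% |
| Some stage falls wholly in one arm | 23.6% | 23.5% |

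The second event depends heavily on the assumed split, ranging from 1.6% (9/9/9/9) to 75% (2/20/12/2). The equivalence itself needs no assumption about stage counts.

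**3. Arm sizes at 36, exact binomial.** P(18:18) = 13.2%. P(smaller arm 14 or fewer) = 2·P(X ≤ 14) = 24.3%. Mean gap between arms = 4.75 patients.

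**4. H&Y balance.** With a share p at stage III-IV, the SD of the difference between arms is roughly √[p(1 − p)(1/18 + 1/18)]. For p = 16/36 this is √(0.2469 × 0.1111) = 16.6 points. Exact enumeration, allowing for random arm sizes, gives:

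| Assumed split | Stage III-IV of 36 | SD of difference (points) | P(gap of 20 points or more) |
|---|---|---|---|
| 4/16/12/4 | 16 | 17.1 | 25.6% |
| 9/9/9/9 | 18 | 17.2 | 24.4% |
| 2/20/12/2 | 14 | 16.7 | 25.3% |

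**5. Power at 30 evaluable, d = 1.1, same t-test formula.**

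| Split | δ | Power |
|---|---|---|
| 15:15 | 3.01 | 82.8% |
| 12:18 | 2.95 | 81.3% |
| 11:19 | 2.90 | 80.0% |
| 10:20 | 2.84 | 78.3% |

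Power falls below 80% only at 10:20 or worse, which is 2·P(X ≤ 10) = 9.9% of allocations. The average over simple randomization is 81.5%, about 1.4 points below the balanced figure.

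**6. Both arms reaching 15 evaluable.** With a fixed 18:18 and 15% drop-out, P(Binomial(18, 0.85) ≥ 15) = 0.720 per arm, and 0.720² = 51.9% for both. Under simple randomization it is 25.0%. At 10% drop-out the figures are 81.3% and 43.3%.

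**7. Effect of blocking.** With blocks of 2 and 4 in random order within two strata (I-II and III-IV) and 16 of 36 at stage III-IV, simulation gives an SD of about 2.6 points for the difference in share. A gap of 20 points never occurs, and the arms are never more unequal than 16:20.

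**The case against.** Simple randomization is a legitimate method. It introduces no bias and does not inflate type I error. This stands: a reader might infer that the trial is invalid, and nothing in the article supports that.

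The power argument is weak. A reader might infer that unequal arms leave the trial underpowered, but on the plan's own 1.1 SD even 12:18 stays above 80%. A lower starting power of 75.3% appears if the 10-point difference is divided by the 10-point SD, giving 1.0 SD. That is a separate inconsistency in the sample size section and not an effect of randomization. A reader might also infer that blocking would secure 15 evaluable per group; step 6 shows that drop-out alone defeats this in nearly half of cases at 15%.

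The analysis gives some cover. Baseline DextQ-24 is in the primary model and may absorb part of an H&Y imbalance, and H&Y adjustment is named as a possible supportive analysis. Both points stand, but the second is optional and neither replaces balance by design. The article gives no figure for the prognostic value of H&Y beyond baseline DextQ-24, so the effect of an imbalance on the treatment estimate cannot be sized.

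Finally, this is a journal article and the system configuration is not shown. *Simple* may be loose wording for a blocked list, so the article does not prove that patients were allocated without restriction. The sentence needs correcting or the method needs changing in either case, but the configuration has to be checked first.

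**Conclusion.** The point holds as a defect in the stated allocation method, and it should be fixed. As written, the stratification secures neither H&Y balance nor near-equal arms, and the primary model does not make up for the missing H&Y balance. The equivalence is exact. The arm-size figures (13% for 18:18; 24% for a smaller arm of 14 or fewer) rest only on 36 patients and literal simple randomization. The H&Y figures (SD about 17 points; 24-26% chance of a gap of 20 points or more) rest on assumed stage counts but hardly vary across the three splits. The cost is mainly in balance and credibility. Power loses about 1.4 points on average, calculated with an unadjusted t test.

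**What to change.** 1. Confirm with the external trial unit which method is set up in SecuTrial.
2. If it is already blocked, correct the word *simple* and describe the restriction.
3. If it is simple randomization and recruitment continues, switch the remaining allocations to concealed permuted blocks of randomly varying size within H&Y strata, keeping allocations already made. Collapsing to stages I-II and III-IV is a sensible option with 36 patients. Add the H&Y stratum as a covariate to the primary ANCOVA, fixed before any outcome data are examined.
4. If enrolment is complete, describe the allocation as simple randomization and make the H&Y-adjusted analysis a definite, prespecified analysis.

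The cost is one configuration change by the trial unit, a short amendment and, with two strata, one degree of freedom in the model. The downside is some predictability at block ends in a single-centre trial where only patients are blinded. Random block sizes, concealment and recruiters who take no part in assessment or treatment limit this without removing it. The change does not by itself guarantee 15 evaluable patients per group.

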**Figure 1 F1:**
[figure not shown]
Design of study: T0 baseline assessment, T1 end of training, T2 follow-up after 3 months. ADL, activities of daily living; QoL, quality of life.

### Participants

The patients are recruited by two investigators ([name]), not involved in the assessment and treatment procedures, at the Neurocenter, Lucerne Cantonal Hospital, Switzerland. Inclusion criteria are confirmed PD according to the brain back criteria (37); H&Y I to IV (36); age 50–90 years old; written and signed informed consent and experiencing dexterous difficulties in performing ADL. Exclusion criteria are significant medical, psychiatric comorbidity including dementia as defined by Montreal Cognitive Assessment (MOCA <21) (38); inability to understand the scope of the study and to follow the study procedures according to the protocol, e.g., filling out questionnaires and participating in another intervention study. Exclusion criteria for TMS use are current pregnancy, personal history of epilepsy or seizures, and any psychiatric, neurological, or medical history other than PD. All data related to the study will be collected at the outpatient neurorehabilitation center, Lucerne Cantonal Hospital.

### Sample Size Calculation

The significance level alpha is defined as 0.05 (two-tailed) for detecting a mean difference between groups on the primary outcome being the Dexterity Questionnaire 24 (DextQ-24) (4) in favor of the real iTBS-VBT dexterity group. Based on previously observed data one may assume a within-group standard deviation of up to 10 points. The study is designed to detect a mean difference of 10 or more points, which exceeds the MDC95 of 8 points found in our validation study (4). A total sample size of 30 evaluable subjects, 15 per group, is required to detect a mean difference of an at least 1.1-fold within-group standard deviation with a target power of at least 80%. Considering a maximal drop-out rate of 15%, we aim to recruit 36 patients in total.

In any case, patients who do not complete the training sessions and/or even decide to drop out of the study for whatever reason will be encouraged to continue to participate in the scheduled assessments for at least T1 (and/or a time point prior to the individual end of the study) and ideally to provide a postbaseline assessment for at least the primary endpoint.

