### Statistical Analysis

Descriptive statistics are used to present baseline characteristics and results of outcome measurements. In order to investigate the treatment effect for the primary endpoint, a hierarchical testing strategy is applied. For DextQ-24 at T1, an ANCOVA model is used with a fixed effect for treatment and the baseline (T0) value of DextQ-24 as a covariate. If a treatment effect at T1 could have been shown (null hypothesis rejected), the same approach will be performed for DextQ-24 at T2 in order to see whether the treatment effect is sustainable. An estimate for the treatment effect will be derived from the model together with a corresponding 95% confidence interval. As a postestimation procedure effect size measures such as (partial) eta square with corresponding 95% intervals will be provided. In an exploratory manner, the secondary endpoints are tested utilizing the same methodology. As a sensitivity analysis, e.g., to explore the robustness of the results in case of missing values, the primary and secondary endpoints are analyzed using linear mixed effects models with fixed effects for treatment, time point, interaction of treatment and time point, baseline value as a covariate and with subject as a random effect. Estimates for the treatment effects at T1 and T2 with corresponding 95% confidence intervals can be obtained as contrasts derived from these models. Further supportive analyses to check the robustness of the treatment effect estimators can be performed by adjusting the model from the primary analysis for the stratifying variable, namely the H&Y scale.

According to the treatment policy strategy (Intention to treat (ITT) principle) every randomized PD patient, including the drop-outs, is included for final evaluation. For all analyses the level of significance is set to alpha = 0.05 (two-tailed). Statistical analyses are performed using Stata (Version 16.1 or later, StataCorp, College Station, Texas, USA).

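### The sample size paragraph names a 10-point target with an SD of up to 10 (1.0 SD at that bound) but sizes the trial for 1.1 SD, and the two figures need reconciling

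*Protocol article*

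**What the plan says.** Three statements in the Sample Size Calculation section of the protocol article bear on this.

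- On variability: "one may assume a within-group standard deviation of up to 10 points".
- On the target: "The study is designed to detect a mean difference of 10 or more points".
- On the size: 30 evaluable patients, 15 per group, is the number that "is required to detect a mean difference of an at least 1.1-fold within-group standard deviation with a target power of at least 80"%.

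The test is two-sided at 0.05. Allowing for at most 15% drop-out, the plan recruits 36. The Trial Design section gives 1:1 allocation. For the primary endpoint at T1, the Statistical Analysis section states that "an ANCOVA model is used with a fixed effect for treatment and the baseline (T0) value of DextQ-24 as a covariate". The sample size section gives no baseline-to-follow-up correlation and no SD other than the upper bound.

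**The concern.** At the only SD the paragraph gives, a 10-point difference is 1.0 SD. The size is then worked out for 1.1 SD, which is 11 points at that SD. Someone reading the paragraph straight through will take 10 points as the difference the trial can detect with 80% power, but the calculation behind the 15 per group does not deliver this at the SD bound.

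The primary endpoint is tested hierarchically. The T2 comparison proceeds only if the T1 null hypothesis is rejected, so T1 power governs the whole confirmatory sequence. If T1 is not significant, the stated detectable difference is one of the figures readers will use to judge what the trial could have seen.

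**Working it through.** **Inputs.** From Sample Size Calculation: two-sided alpha 0.05; SD up to 10; target difference 10 or more points; standardised difference 1.1; 15 evaluable per group; power at least 80%; drop-out 15%; 36 recruited. From Trial Design: 1:1 allocation.

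**Formula.** For a two-sample t-test with n per group and standardised difference d, power is the probability that a noncentral t variable with 2n − 2 degrees of freedom and noncentrality d × √(n/2) falls outside the two-sided 5% critical values.

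**Step 1: reproduce the plan's figure (d = 1.1).**

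- n = 14: noncentrality 1.1 × √7 = 2.910; power 79.99%, just short of 80%.
- n = 15: noncentrality 1.1 × √7.5 = 3.012; power 82.8%.

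The smallest size reaching 80% is therefore 15 per group, or 30 in total, as stated. Drop-out: 30 / 0.85 = 35.3, rounded up to 36, also as stated. A normal approximation gives 13 per group (26 in total) and does not reproduce the plan, so the t-test is taken as the plan's method.

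**Step 2: the same method at the stated target and SD bound.** d = 10 / 10 = 1.0; noncentrality √7.5 = 2.739; power with 15 per group is 75.3%, which is 80 − 75.3 = 4.7 percentage points short. The normal approximation gives 78.2%, also below 80%.

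**Step 3: what 15 per group does detect with 80% power.** Solving for d gives 1.060.

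- At SD 10 the detectable difference is 1.060 × 10 = 10.6 points.
- For a 10-point difference the SD must be at most 10 / 1.060 = 9.4.
- A 10-point difference is at least 1.1 SD when the SD is at most 10 / 1.1 = 9.1.

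Power for 10 points with 15 per group:

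| SD | Power |
|---|---|
| 8 | 91.0% |
| 8.5 | 87.5% |
| 9 | 83.6% |
| 9.5 | 79.5% |
| 10 | 75.3% |

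**Step 4: the gap in patients.** At d = 1.0, 16 per group gives 78.1% and 17 per group gives 80.7%. That is 34 evaluable, and 34 / 0.85 = 40 recruited, against 30 and 36 in the plan.

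**Step 5: the planned ANCOVA (assumption).** Suppose the SD of 10 refers to raw scores and r is the correlation between baseline and T1. The residual SD is then 10 × √(1 − r²), with 27 degrees of freedom. The article gives no r, so a range is shown for 10 points with 15 per group:

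| r | Power |
|---|---|
| 0 | 75.2% |
| 0.3 | 79.0% |
| 0.4 | 82.1% |
| 0.5 | 86.2% |

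Power reaches 80% at r = 0.335, or about 0.34.

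**The case against.** The best reply is that the formal sample size sentence is correct as it stands. It attaches the 80% to 1.1 SD, and that reproduces exactly. A reader might infer that the article claims 80% power for 10 points, but it never says so in one statement; the inference comes from joining adjacent sentences. This stands, and it limits the finding to figures that do not fit together.

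Second, the inputs are bounds. The SD is a ceiling, and the differences are minimum values. At any SD of about 9.1 or less, 10 points is at least 1.1 SD and the statements agree. The power shortfall appears only above about 9.4, at the top of the permitted range. This also stands. However, an SD bound is normally given so that the design holds at it, and the paragraph offers no lower value.

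Third, a reader might infer that the trial is underpowered. The documents do not support this, because a baseline-adjusted analysis may recover more than the missing power (Step 5). Sizing on an unadjusted t-test and then analysing by ANCOVA is a common conservative choice, not an error. Attrition could also be lower than allowed for. The Discussion expects no more than 10% drop-out: 36 × 0.9 = 32.4, so about 16 per group and 78.1% at 1.0 SD. With all 36 evaluable (18 per group) power would be 83.0%. The plan, however, counts on 30.

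Finally, it is tempting to object to the comparison of the 10-point target with the MDC95 of 8 points. That remark does not determine the sample size, so it is no part of this point.

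**Conclusion.** The inconsistency is real but modest. The stated target at the stated SD bound is 1.0 SD, while the size rests on 1.1 SD. By the method that reproduces the plan's own 15 per group, power at 10 points and SD 10 is 75.3%, not 80%, and the 80% detectable difference is 10.6 points, not 10.

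This rests on an unadjusted two-sample t-test, 15 evaluable per group and an SD at its upper bound. It no longer applies if the SD is about 9.4 or less. It would also be met under the planned ANCOVA with a correlation of about 0.34 or more, which is an assumption outside the article. The justification as written therefore does not support 80% power for the 10-point target over the whole stated SD range. Whether the planned analysis falls short cannot be concluded from the document. This is a clarification to make, not a flaw in design or conduct.

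**What to change.** Keep 36 patients and rewrite the paragraph so that difference, SD and power agree. Either of these would do:

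- **Unadjusted statement:** 15 evaluable patients per group give 83% power for 11 points (1.1 SD) and 75% for 10 points at an SD of 10, two-sided 0.05, unadjusted; 80% power for 10 points requires an SD of about 9.4 or less.
- **ANCOVA-based statement:** give the baseline-to-T1 correlation assumed and its source, confirm that the SD of 10 refers to raw scores, and report the resulting power for 10 points. A correlation of about 0.34 or more is needed for 80% at SD 10.

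The cost is one paragraph of wording. The stated power becomes slightly less favourable, or is tied to an explicit assumption. No patients are added and the analysis does not change.
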